### Statistical analysis

2.11

These models' adjusted intervention effects and 95% confidence interval and *p* values will be provided. Statistical significance will be determined by a two‐sided *p* value > 0.05. Statistical analysis will be conducted to understand the characteristics of patients with missing data.

Using SPSS's multiple imputation approach, missing data at the case level will be imputed. For the statistical analysis, SPSS V.22 will be used.

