### Sample size

2.5

With a significance level of 5%, statistical power of 80%, a correlation coefficient of at least 0.3 between the scales, and three measurements of the results—once at baseline and twice after randomization—repeated measures analysis will be used to calculate the sample size. The results of relevant publications will be used as the foundation for the analysis of covariance (ANCOVA) for various indicators. The sample size was calculated using the Sampsi module and the minimum clinically important difference (MCID) effect technique in the Stata 2015 environment. Consequently and based on the enormous sample size available for the quality of life index and accounting for the likelihood of a 20% dropout for each of the three measurements of the outcome, the sample size for this research is 105 participants in each group and 210 participants will be recruited.

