### Data collection and study outcomes

2.9

Table 1 shows the data extraction procedure.

**Table 1 hsr22109-tbl-0001:** The procedure of data collecting.

Measure	Measurement method
Primary outcomes	
Quality of life	HRQOL will be measured using the IBDQ^20^ The IBDQ contains 32 items divided into four health subdimensions: bowel symptoms, systemic symptoms, social functioning, and emotional function. The total score ranges from 32 to 224, and a higher score indicates a better quality of life.^20^, ^21^ A clinically significant change score is +16.^22^, ^23^, ^24^, ^25^
Disease activity scores	Disease activity scores are calculated using the HBI^26^ for participants with CD and the SCCAI^27^ for participants with UC/indeterminate colitis. Patients with CD and an HBI < 5 will be considered to be in clinical remission, whereas patients with scores of 5–7, 8–16, or >16 will be classed, respectively, as having mild, moderate, or severe activity.^26^ For patients with UC, clinical remission will be defined as an SCCAI ≤ 2, whereas values of 3–5 or >5 points will be classed as mild‐to‐moderate or severe activity.^28^
Anxiety and depression	Hospital Anxiety and Depression Scale (HADS): The 14 items on the HADS are equally divided between the HADS‐Anxiety and HADS‐Depression subscales. Subscale scores of 8–10 are categorized as borderline and 11–21 as clinical.^29^, ^30^ A clinically significant change score is −1.5 to −2 points.^31^, ^32^
Secondary outcomes	
Self‐efficacy	Self‐efficacy will be measured with the 29‐item inflammatory bowel disease self‐efficacy scale (IBD‐SES)^33^ Questions are grouped into four domains: managing stress and emotions, managing medical care, managing symptoms and disease, and maintaining remission. Overall scores on the IBD‐SES range from 29 to 290, with higher scores indicating higher self‐efficacy and thus better self‐management and greater patient empowerment.
Patient knowledge	As assessed by the IBD‐KNOW, patient knowledge will be compared between groups. The total score ranges from 1 to 24, and a higher score indicates a higher disease knowledge.^34^
Patient satisfaction (user experience)	Using a 5‐point figurative scale from 1 (*very satisfied*) to 5 (*not satisfied*).

*Note*: Follow‐ups will be done at 0, 12, and 24 weeks after randomization except for the last item.

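### The only stated significance criterion has its inequality reversed: p above 0.05 instead of below 0.05

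*Protocol article*

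**What the plan says.** Section 2.11 of the protocol article states the criterion in one complete sentence: "Statistical significance will be determined by a two‐sided *p* value > 0.05". Just before it, the same section says what will be reported from the models: "adjusted intervention effects and 95% confidence interval and *p* values will be provided".

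Section 2.5 gives the error rates used for the design: "With a significance level of 5%, statistical power of 80%, a correlation coefficient of at least 0.3 between the scales". From these the section arrives at 105 participants per group.

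Sections 2.10, 2.11.1 and 2.11.2 describe regression and repeated measures models but give no threshold. The sentence in section 2.11 is therefore the only place where the article says when a result counts as significant.

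**The concern.** A two-sided test at the 5% level rejects the null hypothesis when the p value is small. The article says the reverse, so its decision rule disagrees with its own design level and with the confidence intervals that will stand beside the p values.

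The sentence is in the general part of the statistical section, so it governs all three primary outcome domains in Table 1 (quality of life, disease activity, anxiety and depression) and the secondary outcomes. Section 1.3 says that this paper explains the protocol and that a second paper will report the results. This is thus the public text against which the results will be checked, and no sensible results paper could follow the rule as it stands.

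**Working it through.** **Inputs**

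- Rule as written: two-sided, significant if p > 0.05 (section 2.11).
- Design significance level: α = 0.05 (section 2.5).
- Design power: 1 − β = 0.80 (section 2.5).
- Confidence level reported with the p values: 95% (section 2.11).

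**Step 1. The plan's own figure, with the sign in the usual direction.** For a two-sided test that rejects when p < 0.05, the normal critical value is 1.96, and the type I error is 2 × (1 − Φ(1.96)) = 0.05. This reproduces the 5% in section 2.5. Power at the design alternative is 0.80 by construction.

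**Step 2. Type I error of the rule as written.** Under the null hypothesis the p value is uniform on (0, 1). Hence P(p > 0.05 | null) = 1 − 0.05 = 0.95.

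**Step 3. Chance of declaring significance at the design alternative.** There P(p < 0.05) = 0.80, so P(p > 0.05) = 1 − 0.80 = 0.20.

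| Rule | No effect | Design alternative |
|---|---|---|
| p > 0.05 (as written) | 95% | 20% |
| p < 0.05 (sign reversed) | 5% | 80% |

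These are figures per test. The second column applies to the comparison for which the trial was sized, which section 2.5 ties to the quality of life index.

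**Step 4. Agreement with the confidence interval.** A 95% interval from the same model excludes the null value when p < 0.05 and includes it when p > 0.05. Under the written rule an effect would be called significant exactly when its interval includes no effect.

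**Step 5. Could a one-sided reading rescue it?** No. The sentence specifies a two-sided p value, and in any case the fault lies in the direction of the inequality, not in the number of tails.

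**Step 6. Could it be a fault in reading the PDF?** This cannot be fully excluded, but nothing points to it. The sentence is intact. In Table 1 the signs in the activity cut-offs (HBI < 5 for remission, > 16 for severe; SCCAI ≤ 2 for remission) all run in the sensible direction.

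**Step 7. Effect on sample size.** None. The calculation in section 2.5 uses the 5% level, not the misprinted sentence. The 105 per group cannot be fully re-derived, since no standard deviation is given, but the point does not depend on it.

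**The case against.** The strongest reply is that the slip corrects itself. The 5% level in section 2.5 and the 95% intervals in section 2.11 fit only p < 0.05. No analyst or reader would apply the opposite rule, and no part of the design, data collection, model or estimate depends on this character. The 95% and 20% are then properties of a hypothetical rule, not of the trial. This stands as far as practical harm goes: the harm is small. It does not make the sentence right, and no other sentence in the article states the rule correctly.

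A reader might also infer that the literal rule turns all null results into successes and all real effects into failures. The arithmetic does not support that. Even read literally, 5% of tests with no effect would not be declared significant, and 20% of tests at the design alternative would be.

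Nor does this point call for naming a single primary outcome or adding a multiplicity rule. Table 1 lists three primary outcomes, and inserting a single one into the corrected sentence would create a new conflict with that table. Finally, no SAP is shown, so it cannot be assumed that one repeats the slip.

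**Conclusion.** The sentence is wrong as written and contradicts both the 5% level in section 2.5 and the confidence intervals in section 2.11. Taken literally it gives each test a 95% type I error and a 20% chance of significance at the design alternative, where 5% and 80% were intended. The first figure rests only on the uniform distribution of the p value under the null hypothesis. The second takes the stated 80% power at face value.

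It is almost certainly a typographical slip. A reader should not conclude that the trial will be run with a 95% error rate: the article's own design level shows which direction was meant. It deserves correction because it is the only decision threshold stated.

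**What to change.** In section 2.11, replace the greater-than sign with a less-than sign, so that significance means a two-sided p value below 0.05. Leave the rest of the sentence as it is. Issue a correction to the published article before the results are reported, and check any SAP for the same slip.

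The cost is one character and a short correction notice. The sample size, the data collected and the models stay as they are. How to handle multiplicity across the three primary outcomes should be considered separately and not folded into this correction.

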#### Primary study analysis

2.11.1

The initial outcome analyses investigated mean disease activity measures within disease type at baseline and each of the measurement; repeated measures analysis of variance (ANOVA) will be used to compare the intervention groups and standard care at these time points. Also, repeated measures ANOVA will be used to compare each group's change from baseline at 12 and 24 weeks, within disease type. The two groups will be combined in the same analyses if a low variation is identified. Plots of mean outcome values in each group will be examined for indications of change patterns. Similar analyses will be used for quality of life and anxiety and depression scores by groups and for all participants.

Furthermore, the primary goal of these repeated measures analyses will be to detect differences between the intervention groups in patterns of change from baseline across the 6 months. Regression diagnostics will be examined to detect outliers, influential observations, and other deviations from assumptions for all models. To detect potential bias by analysis of only the collected data, participants with and without data at a given time will be compared to determine the baseline characteristics of those who did not provide complete data.

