## CONCLUSIONS

4

Our primary aim was to assist other researchers in developing tele‐management interventions, selecting appropriate methods for remotely measuring health outcomes, and identifying patient groups that would benefit from this approach in future IBD studies. The outcomes of our trial will demonstrate the impact of the gamified mobile‐based self‐management system on disease activity, quality of life, and anxiety and depression by means of interactive care and patient empowerment. It is imperative to undertake additional studies to authenticate the effectiveness of the *MY IBD BUDDY* tele‐management program in other specific patient groups, such as those with uncomplicated diseases, limited access to medical care or social support, and patients who cannot attend specialized IBD clinics.

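### Several primary scores share one 5% threshold with no order or combination rule, so even on the narrow reading the chance of a false positive primary result is about 11% to 23%

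*Protocol article*

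**What the plan says.** Table 1 (section 2.9) places three rows under primary outcomes.

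- Quality of life: "HRQOL will be measured using the IBDQ".
- Disease activity: the HBI in Crohn's disease (CD) and the SCCAI "for participants with UC/indeterminate colitis". These are two instruments in two separate sets of patients.
- Anxiety and depression: "Hospital Anxiety and Depression Scale (HADS): The 14 items on the HADS are equally divided between the" anxiety and depression subscales, so this row holds two scores.

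No row is marked as the main one.

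Section 2.11.1 compares the arms on disease activity at each measurement, and on change from baseline at weeks 12 and 24, within disease type. The disease types are pooled if variation is low, and no criterion is given for this. It then adds: "Similar analyses will be used for quality of life and anxiety and depression scores by groups and for all participants". It also states the main purpose of these models, which is to find arm differences in the course of change from baseline over the 6 months.

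Section 2.11 gives one decision rule: "Statistical significance will be determined by a two‐sided *p* value > 0.05". The direction of the sign is evidently a misprint, and the rule is read here as p below 0.05.

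Section 2.5 opens "With a significance level of 5%, statistical power of 80" per cent, and reaches 105 participants per group "based on the enormous sample size available for the quality of life index".

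**The concern.** The trial is sized at a 5% level on one outcome, but the analysis sections let any of several primary scores be declared significant at that same level. Without an order of testing, an adjustment or a rule for combining the results, one significant score among several could be reported as a positive primary result. The 5% in section 2.5 would then be the error rate of each test and not of the trial's primary conclusion.

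This matters because the article makes efficacy claims. Section 2.1 states directional hypotheses and an aim of evaluating efficacy, and section 4 says "The outcomes of our trial will demonstrate the impact of the gamified" system on disease activity, quality of life, anxiety and depression.

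**Working it through.** **Stated figures.** The article gives no overall error rate for the primary outcomes, so there is none to reproduce. The 105 per group cannot be checked either, because no IBDQ standard deviation is given. The point does not depend on it.

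**Inputs from the article.** Two-sided 5% per test (sections 2.5 and 2.11); scores IBDQ, HBI or SCCAI, HADS anxiety and HADS depression (Table 1); visits at weeks 12 and 24 and the disease-type split (section 2.11.1).

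**Inputs assumed.** The article does not give the correlation among the test statistics. The ranges used are 0 to 0.8 between scores and 0.3 to 0.7 between visits. CD and ulcerative colitis (UC) are taken as equal in size and independent, being different patients.

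**Counting the tests.**

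- Narrow reading, one arm comparison per score over 6 months: 4 tests if disease activity is pooled, 5 if HBI (CD) and SCCAI (UC) are tested separately.
- Adding disease type for the other three scores: 2 + 3 × 3 = 11 tests.
- Adding both visits: 11 × 2 = 22 tests, or 12 × 2 = 24 if a pooled disease activity test is included.

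**Independent tests.** The chance of at least one false positive among k tests is 1 − 0.95^k.

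- k = 4: 1 − 0.95^4 = 18.5%
- k = 5: 1 − 0.95^5 = 22.6%
- k = 22: 1 − 0.95^22 = 67.6%
- k = 24: 1 − 0.95^24 = 70.8%

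Counting only the three rows of Table 1 gives 1 − 0.95^3 = 14.3%.

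**Correlated tests.** Multivariate normal test statistics were simulated with no effect on any score (400,000 draws per setting). The overall statistic is the equally weighted combination of the CD and UC statistics.

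| Set of tests | Correlations of 0.5 | Range over the assumed correlations |
|---|---|---|
| 4: one per score, all patients | 16% | 11% to 18.5% |
| 5: HBI, SCCAI, three scores in all patients | 20% | 16% to 23% |
| 11: adds CD and UC for the other scores | 32% | 24% to 37% |
| 22 to 24: adds both visits | 51% to 52% | 37% to 61% |

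The top of the last range (61%) is below the independence figures because visits, and overall and disease-type results, are correlated even when the scores are not.

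**Power under two remedies.** The planned standardised effect for 80% power at two-sided 5% is 1.960 + 0.842 = 2.802. If IBDQ is tested first at 0.05, its power stays at 80%, and the gate stays closed in 100 − 80 = 20% of trials with the planned effect. If all five scores stay primary under Holm, the first step is at 0.05/5 = 0.01, with critical value 2.576. If IBDQ has to pass at that step, its power is Φ(2.802 − 2.576) = Φ(0.226), about 59%. This is the worst case, because Holm relaxes the level once another score is significant.

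**The case against.** **The trial is called exploratory** in the abstract and in section 2.4, and no success rule is stated. The any-one-of-several error rate matters only if one positive score counts as success. If every score had to be significant, the error would not exceed 5%. This softens the consequence. It does not remove it, because the article states no such requirement and makes efficacy claims.

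**An analysis plan that is not shown may adjust for multiplicity.** That is possible, and the absence of an adjustment method from an article is not in itself a fault. However, this document itself fixes the list of primary outcomes and a single threshold, and sizes the trial on only one of those outcomes.

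**The widest count is too strong.** A reader might infer that the false positive risk exceeds 50%. The article does not support that as a firm figure, for three reasons.

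- Section 2.11.1 names the course of change over the 6 months as its main target, which points to one comparison per score and not separate tests at each visit.
- In "Similar analyses will be used for quality of life and anxiety and depression scores by groups and for all participants", the word 'groups' may mean disease types, which is natural after the sentence on combining the two groups. It may also mean study arms, as elsewhere in that paragraph.
- Even on the full count, stronger correlations bring the figure below 50%.

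**Choosing IBDQ as the gate is partly a preference.** Section 2.1 names disease activity first. The ground for IBDQ is that quality of life settled the sample size. A reader might also infer that section 2.5 sized the trial on the difference averaged over weeks 12 and 24. It mentions one baseline and two later measurements and an analysis of covariance, but does not state that contrast.

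**Conclusion.** The point holds in a limited form. The primary outcome list, the single threshold and the sizing on one outcome do not fit together. On the reading most favourable to the plan, with four or five tests, the chance of at least one false positive primary result is about 11% to 23%, which is at least twice the stated 5%. This rests on treating any one significant primary score as a positive result, on testing the two HADS subscales separately, and on the assumed between-score correlations.

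The higher figure of about 37% to 61% applies only if every visit and disease type is tested. It shows what the present wording permits and is not an established error rate. Pooling disease types without a stated criterion adds flexibility that none of these figures includes.

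**What to change.** 1. Name IBDQ total as the single primary outcome. Test it by the arm comparison of change from baseline over the 6 months, at two-sided 0.05.
2. If that test is significant, test HBI (CD), SCCAI (UC), HADS anxiety and HADS depression with Holm at 0.05. The first Holm step is 0.05/4 = 0.0125.
3. Report single-visit and disease-type results as estimates with 95% confidence intervals, without claims of significance.

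This holds the familywise error at 5% and needs no extra patients or data. It costs a change to the analysis text and an update of the registered outcome list, since disease activity and HADS would no longer be primary. The main statistical cost is that these scores get no formal test when IBDQ fails, which at the stated power happens about 20% of the time even with the planned effect.

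If the sponsor prefers to keep all the scores primary, Holm across them also holds 5%. The price is lower power for IBDQ: about 59% instead of 80% in the worst case with five tests.

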### Data management

2.10

First, the characteristics of the patients in the test and control groups will be documented, and any differences between the groups will be assessed using tests to measure variations in means or proportions. Second, the intergroup variations in disease outcomes will be assessed using multivariable linear regression which will be adjusted for the following stratification criteria: subtypes of IBD (CD or UC), disease activity at baseline (remission or active), age (numerical), sex (male or female), disease duration (numerical), smoking (nonsmoker, active smoker, or ex‐smoker), and educational level (five levels). For missing outcomes and variables, the multiple imputation approach will be used to impute the missing data. Results will be adjusted for age, sex, and illness duration, disease activity at baseline, educational attainment, and stratification criteria.

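### IBDQ and HADS are to be compared by disease group and overall, with an undefined pooling rule and no estimate of whether the effect differs between CD and UC; read side by side, disease-specific verdicts would mislead in about half of trials with equal benefit

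*Protocol article*

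**What the plan says.** Section 2.11.1 (Primary study analysis) uses repeated measures ANOVA to compare the arms on disease activity, including "change from baseline at 12 and 24 weeks, within disease type". It then says that the two groups, which here can only be the two disease types, will be analysed together if their variation is low. It names no statistic or threshold and does not say what the variation is of. For the remaining primary outcomes it states: "Similar analyses will be used for quality of life and anxiety and depression scores by groups and for all participants".

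Section 2.10 (Data management) describes a linear regression for differences between the arms, with adjustment for a list that begins "subtypes of IBD (CD or UC), disease activity at baseline (remission or active" and goes on to other baseline factors. Disease type is one adjustment term among several, and no product of arm and disease type is mentioned. Section 2.7 makes disease type a randomization stratum.

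Section 2.5 (Sample size) sizes the trial on quality of life for the whole sample, 105 per arm, starting from "With a significance level of 5%, statistical power of 80%, a correlation coefficient of at least 0.3 between the scales". Section 2.11 attaches p values and a two-sided significance verdict to the results.

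**The concern.** Followed as written, the plan yields for each of IBDQ, HADS-anxiety and HADS-depression one test in CD, one in UC and one overall. A significant result in one disease beside a non-significant result in the other does not show that the effects differ. Each disease holds only part of the sample, so each test is much weaker than the overall test, and disagreement between them is common even when the effects are identical.

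The pooling rule does not fill the gap. It is not said to concern the treatment effect, and it has no criterion. If the word similar carries it over to IBDQ and HADS, it is also unclear whether the all-participant analysis of those scores is unconditional.

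At stake is how the results are read. A report showing a benefit in one disease and not in the other could steer later studies or use of the app, although the data may fit an equal effect. IBDQ and HADS have the same scale in both diseases, so the difference in effect can be estimated directly.

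**Working it through.** **Inputs.** From the article: two-sided 5% level ("Statistical significance will be determined by a two‐sided" p value; the inequality sign printed after it is a separate slip and does not matter here), power 80%, correlation 0.3, "three measurements of the results—once at baseline and twice after randomization", and 105 per arm with 20% dropout. Assumed: a CD:UC split of 50:50, varied below; the same true effect and SD in both diseases; one arm contrast per test, by normal approximation.

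**The plan's own figure.** With repeated-measures ANCOVA the variance factor is (1 + 0.3)/2 − 0.3² = 0.56, and n per arm = 2 × 0.56 × (SD × 2.802/δ)². Section 2.5 gives neither δ nor SD. Table 1 says for the IBDQ: "A clinically significant change score is +16". Taking δ = 16 and solving backwards, 105 per arm implies an SD of 49.5 if 20% is lost once (84 per arm), 44.2 if lost twice (67.2) and 39.6 if lost three times (53.76). So 105 can be neither confirmed nor refuted. The figures below do not need the SD, because they start from the stated power.

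**Power in each disease.** Overall noncentrality = 1.960 + 0.842 = 2.802. In a disease with share s of the sample it is 2.802 × √s, and power = Φ(2.802√s − 1.960). The two diseases are independent, so P(exactly one significant) = p₁(1 − p₂) + p₂(1 − p₁).

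| Split | Power in each disease | Exactly one significant |
|---|---|---|
| 50:50 | 0.508 / 0.508 | 0.500 |
| 60:40 | 0.583 / 0.425 | 0.512 |
| 70:30 | 0.650 / 0.335 | 0.549 |
| 80:20 | 0.707 / 0.240 | 0.608 |

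At 50:50: 2 × 0.508 × 0.492 = 0.500; both tests are significant in 0.258 of trials and neither in 0.242. Among trials with a significant overall result, a simulation of 1,000,000 draws gives a split verdict in 57% at 50:50 and 71% at 80:20.

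**Sensitivity to power.** If the overall power for a score is 90%, the 50:50 figure is 47%; at 70% power it is 49%.

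**Comparator.** With equal effects, an arm-by-disease-type test at the 5% level wrongly signals a difference in 5% of trials per score.

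**Precision of the interaction.** SE(interaction)/SE(overall) = 1/√(s(1 − s)): 2.0 at 50:50 and 2.2 at 70:30. With 84 evaluable per arm the overall SE is √(2 × 0.56/84) = 0.115 SD, so the 95% half-width for the CD-minus-UC difference is 1.96 × 2 × 0.115 = 0.45 SD.

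**The case against.** **The groups may be the study arms.** The article mostly uses group for intervention and control, including in the sentence on plots just before the quoted one, and its own term for CD and UC is disease type. This is a fair objection. Disease groups is still the better reading. The phrase is set against all participants, the paragraph works within disease type, and the earlier sentence on combining two groups makes sense only for CD and UC. The wording needs repair on either reading.

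**An interaction term is a detail for the analysis plan.** Partly accepted: an analysis plan that is not shown may contain one, and its absence alone would not be a finding. The point rests on what the article does fix, namely separate comparisons by disease and a pooling condition without a criterion.

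**Nothing says the two verdicts will be compared.** This stands. A reader might infer that the trial means to decide who benefits from two p values, because the Conclusions speak of "identifying patient groups that would benefit from this approach in future IBD studies". That sentence is about helping other researchers. Section 2.1 states efficacy in adults with IBD and no CD-versus-UC hypothesis. The misreading is therefore a risk that the plan leaves open, not a claim that it makes.

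**Combining scores inflates the figure.** One could say that at least one of the three scores gives a split verdict in 69% to 88% of trials (between-score correlation 0.9 to 0). That assumes exactly 80% power for both HADS scores, although quality of life set the sample size, and the upper end needs uncorrelated scores, which is implausible here. The matching error for three interaction tests is about 8% to 14% (1 − 0.95³ = 0.143 if independent), not 5%. The per-score figure is the sound one.

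**Conclusion.** The point holds as a weakness in how disease-specific results are set up. If the CD and UC verdicts on a score are read side by side, an equal benefit would appear confined to one disease in about 50% of trials, or 55% at a 70:30 split, against 5% for an interaction test. This rests on the stated 80% overall power, an assumed CD:UC split, equal effects and SDs, and the reading of the groups as disease groups. The power for HADS is not stated; at 90% the figure is still 47% at an even split.

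A reader might infer that the trial's main comparison is unsound. The documents do not support that: the all-participant analysis is planned, and its result is not affected. Nor does the article commit itself to claiming a differing benefit. The change should be made, because it costs little and closes off a misleading reading.

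**What to change.** In section 2.11.1, for IBDQ, HADS-anxiety and HADS-depression:

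- State that the groups in the quoted sentence are disease types.
- Take the all-participant model, adjusted for disease type, as the result, and say that it does not depend on the rule about low variation.
- Add an arm-by-disease-type term and report the CD-minus-UC difference in effect with its 95% confidence interval.
- Show the CD and UC effects descriptively, without separate significance verdicts.
- State that a differing benefit will be claimed only from the interaction.

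HBI and SCCAI are different scales and stay within disease type.

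The cost is one model term and a few sentences, with no new data or patients; disease type is already a stratification factor. The drawback is imprecision. The interaction's standard error is about twice that of the overall effect (half-width about 0.45 SD under the assumptions above), so it will usually show no clear difference. The report should say that this is not proof of equal effects.

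### The sample size rests on ANCOVA, but the primary analysis is a repeated measures ANOVA of change from baseline; at the minimum correlation of 0.3 this would cut 80% power to about 43–53% for quality of life

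*Protocol article*

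**What the plan says.** Section 2.5 (Sample size) begins "With a significance level of 5%, statistical power of 80%, a correlation coefficient of at least 0.3 between the scales" and counts "three measurements of the results—once at baseline and twice after randomization". It then names the method: "The results of relevant publications will be used as the foundation for the analysis of covariance (ANCOVA) for various indicators". It takes the sample size from the quality-of-life index, allows for 20% dropout, and arrives at 105 per group.

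Section 2.11.1 (Primary study analysis) plans repeated measures ANOVA in two forms: on the means at baseline and each later visit, and on change from baseline at 12 and 24 weeks. It states that "the primary goal of these repeated measures analyses will be to detect differences between the intervention groups in patterns of change from baseline" over the six months. It applies the same approach to quality of life and to anxiety and depression. The baseline score is not named as a covariate.

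Section 2.10 (Data management) describes another model: "the intergroup variations in disease outcomes will be assessed using multivariable linear regression". Its covariates include baseline disease activity in two categories (remission or active), but not the baseline IBDQ or HADS score. Section 2.11 says that adjusted effects, confidence intervals and p values will be reported from these models.

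**The concern.** The method that justified the sample size is not the method assigned to the primary question. ANCOVA uses the baseline score to remove variance. A change score subtracts the whole baseline whatever its correlation with follow-up, so at a low correlation it adds more noise than it removes. A repeated measures ANOVA that includes baseline as one of the responses tests the same change contrasts through its group-by-time term.

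Two things are at stake. First, the 80% need not hold under the analysis named as primary. Second, the article does not say whether the ANOVA in 2.11.1 or the adjusted regression in 2.10 decides the trial, so the same outcome could have two different primary answers.

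**Working it through.** **Inputs.** Power 80% and alpha 5% (2.5). Testing is two-sided: section 2.11 says "Statistical significance will be determined by a two‐sided" p value, although the inequality printed after it is evidently reversed. One baseline and two follow-ups (2.5). Correlation r: "a correlation coefficient of at least 0.3 between the scales", read here as the correlation between any two time points. Sample size 105 per arm with 20% dropout, so 105 × 0.8 = 84 analysed.

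**The plan's own figure.** The 105 cannot be reproduced. Section 2.5 gives no SD and does not state the MCID it used; Table 1 gives +16 for the IBDQ. With +16 and r = 0.3, the number analysed per arm is 2 × 7.849 × 0.56 × SD²/16² (the factors are derived below). Assumed SDs of 30, 40, 45 and 50 give 31, 55, 70 and 86, or 39, 69, 88 and 108 per arm after dividing by 0.8. So 105 per arm would imply an SD of about 49.5 with 84 analysed, or about 39.6 if 20% is lost three times over (105 × 0.8³ = 53.8). The figure is neither confirmed nor refuted. The comparison below does not need it, because SD and effect size cancel.

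**Variance factors** (equal variances and correlations, follow-up mean over two visits):

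- ANCOVA: (1 + r)/2 − r². At r = 0.3: 0.65 − 0.09 = 0.56.
- Change (follow-up mean minus baseline): (1 + r)/2 + 1 − 2r. At r = 0.3: 0.65 + 1 − 0.60 = 1.05.
- Change minus ANCOVA: 1 − 2r + r² = (1 − r)², which is positive for every r below 1. The direction of the loss therefore does not depend on the value of r.

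**Power at r = 0.3.** An N that gives 80% by ANCOVA has noncentrality (1.960 + 0.8416)² = 7.849. Under the change analysis this becomes 7.849 × 0.56/1.05 = 4.186.

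- 1-df change contrast: Φ(√4.186 − 1.960) = Φ(0.086) = 53.4%.
- 2-df group-by-time test, with an equal effect at both visits and so the same noncentrality: 43.2% by noncentral chi-square, 42.9% by noncentral F with 84 per arm.
- To hold 80% on the 1-df contrast, the analysed N must rise by 1.05/0.56 = 1.875, from 84 to about 158 per arm, or about 197 per arm with 20% dropout.

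**Power at higher correlations**, N held at the ANCOVA value for r = 0.3:

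| True r | ANCOVA | Change, 1 df | Group-by-time, 2 df |
|---|---|---|---|
| 0.3 | 80.0% | 53.4% | 43.2% |
| 0.4 | 81.4% | 59.9% | 49.4% |
| 0.5 | 84.3% | 67.8% | 57.3% |
| 0.6 | 88.5% | 77.2% | 67.7% |
| 0.7 | 93.8% | 87.8% | 80.6% |

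The 1-df contrast reaches 80% where (1 + r)/2 + 1 − 2r = 1.5(1 − r) = 0.56, that is r = 0.627. The 2-df test reaches it at about 0.70.

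**Other assumptions varied**, at r = 0.3. If nobody drops out and 105 per arm are analysed, power is 63% (1 df) and 52% (2 df). If the effect at week 24 is twice that at week 12 with the same average, the 2-df test has 55%.

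**The regression in 2.10.** If it compared the mean of the two follow-ups with no baseline adjustment, its factor would be 0.65 and its power Φ(√(7.849 × 0.56/0.65) − 1.960) = 74%. The article does not say whether it averages the visits.

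**The case against.** The strongest reply is that 0.3 is a floor, so 43–53% is the value at the bottom of the assumed range and not the power of the trial. That stands: a reader might infer that the design simply has half the power it claims, and the text does not support that. The correlation is also described as being between scales, so reading it as between time points is an assumption.

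A second reply is that the ANCOVA sentence in 2.5 is loosely worded, next to a mention of repeated measures analysis, and that 105 cannot be traced to any SD or MCID. Sizing on ANCOVA is the natural reading, but the result has to be conditional: if 80% holds by ANCOVA, it does not hold by the change analysis at that correlation. Nor does this show that 105 is wrong.

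Third, the figures must not be carried over to every primary outcome. Quality of life set the sample size; the ANCOVA power for disease activity and HADS at this N is not given.

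Fourth, the adjusted regression may be the analysis meant for reporting, since 2.11.1 describes its own work as initial and 2.11 promises adjusted effects. The low figures belong to the ANOVA and not to that regression. But 2.11.1 carries the primary heading and the stated primary goal, and the regression's remission/active covariate is not an adjustment for baseline IBDQ or HADS. It therefore does not restore the ANCOVA assumption for the outcome that set N.

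Finally, the trial calls itself exploratory, and an unseen analysis plan may hold more detail. That lessens the consequence, but the mismatch lies between two things that the article itself states.

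**Conclusion.** The mismatch is real: the sample size rests on ANCOVA, the primary analysis is an ANOVA of change from baseline, and no stated model uses the baseline IBDQ or HADS score. The change analysis is less efficient than ANCOVA at every correlation below 1.

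The size is conditional. For quality of life, with 0.3 read as the correlation between time points, equal correlations, an equal effect at weeks 12 and 24, and dropout as planned, 80% by ANCOVA corresponds to about 53% (1 df) or 43% (2 df) at the minimum correlation. At 0.5 it is about 57–68%, and 80% or more returns only from about 0.63 (1 df) to 0.70 (2 df). A reader might also infer that section 2.5 powered the arm difference averaged over both visits. That contrast is consistent with an ANCOVA sample size, but the section does not name it.

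**What to change.** In 2.11.1, replace the repeated measures ANOVA as the primary analysis by a model of the week 12 and week 24 scores with the baseline score of the same outcome as a covariate. One example is SPSS MIXED with arm, visit, arm-by-visit, baseline score and the stratification factors. State that this model gives the primary result, and that the ANOVA and the 2.10 regression are supportive.

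Name one primary contrast. The arm difference averaged over weeks 12 and 24 is the natural choice for an ANCOVA sample size; section 2.5 should then say so, and should give the SD, the MCID and which correlation the 0.3 refers to.

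If the change-from-baseline ANOVA is kept as primary, restate the power under that analysis with its correlation assumption.

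The cost is wording. The baseline scores are already collected and SPSS is already the named software. The change should be made before the outcome data are analysed.
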